#### 7.5 Laboratory Method

The laboratory tests that intended to be used for upper (Bronchoalveolar lavage, tracheal aspirate, and Sputum) and lower (Nasopharyngeal swab and oropharyngeal swab) respiratory samples should follow the updated national guidelines. BAL and tracheal aspirate should be 2-3 mL in a sterile, leak-proof, screw-cap container while Sputum collected directly into a sterile, leak-proof, screw-cap container. For the collection of Nasopharyngeal and oropharyngeal, synthetic fiber swabs with plastic shafts should be used. It is not recommended to use swabs with wooden shafts or calcium alginate swabs, which might have a negative impact on PCR results. Swabs should be immediately placed (separate or combined) into a sterile tube containing 2-3 ml of viral transport media (VTM).

Store samples at  $2-8^{\circ}\text{C}$  and ship on an ice pack to the designated laboratory. Samples can be stored at  $2-8^{\circ}\text{C}$  for  $\leq 48$  hours; if longer storage is needed, samples should be stored at  $-70^{\circ}\text{C}$ . If the sample is frozen at  $-70^{\circ}\text{C}$ , ship on dry ice.

Testing will be limited to qualified laboratories with a certified Biological Safety Cabinet Class II (BSC-II ) in a Biosafety level 2 facility (BSL-2) with negative pressure room and those approved by Saudi CDC. Diagnostic RT-PCR will be performed by each hospital's laboratory or the reference/National laboratory of the Saudi Ministry of Health. Additionally, respiratory and blood samples might be sent to King Abdullah International Research Center for further testing. The testing procedure includes extracting ribonucleic acid (RNA) from respiratory specimens using the MagNA Pure 96 Viral NA Kit. The extracted nucleic acids will be tested by rRT-PCR

targeting the upstream SARS-CoV-2 envelope protein gene. The laboratory should follow the Saudi CDC recommendations for Results interpretation of Real-Time RT-PCR and follow the manufacturer recommendations for the defined cut-off CT value for the positive results based on the CT value for each target gene.

## 8. FLOW CHART

Table 4: Flow Chart

|                                                 | Study period |                 |    |     |    |     |    |     |     |     |     |          |
|-------------------------------------------------|--------------|-----------------|----|-----|----|-----|----|-----|-----|-----|-----|----------|
|                                                 | Baseline     | Post allocation |    |     |    |     |    |     |     |     |     | Closeout |
| Timepoint study days                            | D0           | D1              | D2 | D'' | D5 | D'' | D9 | D10 | D'' | D14 | D21 | D28      |
| Enrolment and assignment                 |              |                 |    |     |    |     |    |     |     |     |     |          |
| Eligibility assessment                          | X            | X               |    |     |    |     |    |     |     |     |     |          |
| Informed consent                                | X            | X               |    |     |    |     |    |     |     |     |     |          |
| Randomization                                   | X            | X               |    |     |    |     |    |     |     |     |     |          |
| Baseline data                                   | X            | X               |    |     |    |     |    |     |     |     |     |          |
| Study drug administration                |              |                 |    |     |    |     |    |     |     |     |     |          |
| Favipiravir                                     |              | X               | X  | X   | X  | X   | X  | X   |     |     |     |          |
| Hydroxychloroquine                              |              | X               | X  | X   | X  |     |    |     |     |     |     |          |
| Adverse effect reaction                         |              | X               | X  | X   | X  | X   | X  | X   | X   | X   |     |          |
| Serious adverse event assessment                |              | X               | X  | X   | X  | X   | X  | X   | X   | X   | X   | X        |
| Clinical data collection                 |              |                 |    |     |    |     |    |     |     |     |     |          |
| Seven-category ordinal scale and CRF            | X            | X               | X  | X   | X  | X   | X  | X   | X   | X   | X   | X        |
| Laboratory data collection               |              |                 |    |     |    |     |    |     |     |     |     |          |
| Covid-19 PCR from Respiratory sample *          | X            | X               |    |     | X  |     |    | X   |     | X   | X   | X        |
| CBC, renal profile and LFT on Study Drug | X            | X               | X  | X   | X  | X   | X  | X   |     | X   | X   |          |
| CBC, renal profile and LFT on SoC        | X            | X               |    |     | X  |     |    | X   |     |     | X   |          |

|                                             |   |   |   |   |   |  |  |   |  |  |  |  |
|---------------------------------------------|---|---|---|---|---|--|--|---|--|--|--|--|
| ECG for patient on Study Drug | X | X | X | X | X |  |  | X |  |  |  |  |
| ECG for patient on SoC        | X | X |   |   | X |  |  | X |  |  |  |  |

## 9 STATISTICAL CONSIDERATIONS

### 9.1 General Considerations

This is a randomized, Open-Label trial comparing Favipiravir tables + Hydroxchloroquine tablets standard of care group for the treatment of subjects with moderate to severe SARS-COV-2 infection. The Intention to treat (ITT) analysis will include all subjects randomized. The primary analysis population for the evaluation of both efficacy and safety outcomes will be a modified ITT population, and include all subjects who have been randomized and in which the study drug (Favipiravir tables + Hydroxchloroquine or Standard of care) was started and the patient did not withdraw consent.

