## 3. STUDY DESIGN

This is an Open label, multicenter, randomized controlled clinical trial to evaluate the safety and efficacy of novel therapeutic agents in hospitalized adults diagnosed with COVID-19. It is a multicenter trial that will compare Favipiravir plus Hydroxychloroquine combination (experimental arm) to a control arm.

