#### Reference Therapy:

Standard of care is defined as: Treatment that is accepted by medical experts as a proper treatment for Covid-19 disease. Standard care comprised, as necessary, supplemental oxygen,

noninvasive and invasive ventilation, antibiotic agents, vasopressor support, renal-replacement therapy, extracorporeal membrane oxygenation (ECMO), and antiviral therapy except Favipiravir. Also, it may include intravenous fluids and medications for symptoms relieve.

Although it would not be preferred to use medication that has antiviral activity, the treating physician would have the authority/ autonomy to start the patient on antiviral but not Favipiravir, i.e., Lopinavir–Ritonavir, interferon, ribavirin, Hydroxychloroquine or Remdesivir). Anyone of those medications with possible antiviral activity against SARS-CoV-2 would be accepted to be used in the case that treating physicians thought it would be the best of interest for the patient.

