### 7.3 Treatment assignment

In the participating site, the research coordinator/ principal investigator for the site will check all positive reported COVID-19 by PCR confirmed SARS-coV-2 viral infection. Then an assessment of the eligibility by the research coordinator and assessing inclusion/exclusion criteria. The possible study participant can be assessed in the first 72 hours of admission regarding eligibility. Once eligible, informed consent will be obtained. Randomization will be done in 1:1 whether to intervention or control arm and stratified by the center.

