### 9.2 Sample Size and Power Considerations

#### 9.2.1 Assumptions and Study Hypothesis:

- a. **Time to discharge or clinical improvement by 2 points** in the standard of care arm is expected to be (median: 11 days; Cai Q, Y.M., Liu D, Chen J, Shu D, Xia J, , Experimental Treatment with Favipiravir for COVID-19: An Open-Label Control Study. 2020.).
- b. The exact treatment effect from Favipiravir tables + Hydroxchloroquine is not exactly known but can be approximated using prior clinical studies. A study comparing the effect of Favipiravir to lopinavir/ritonavir on virus clearance has shown a 64% reduction in time to viral clearance in the Favipiravir arm. This was equivalent to a median of 11 days. We assume that clinical improvement might take place a little later to viral clearance and therefore we assume that the treatment arm might result in a minimum clinically meaningful expected reduction of 30% (Median 7.7 days). This is equivalent to a Hazard ratio of 0.7.

- c. We further assume, that 50% of the patients in the control group will have clinical improvement/ discharged and 70% will have clinical improvement/discharged in the treatment arm
- d. It is anticipated that very few of these subjects will be randomized and not start study treatment (and so be excluded from the primary analysis) or be lost to follow-up (and so have missing data for the primary endpoint). Given certain uncertainties however, we have included a nominal 10% drop out rate.
- e. The primary hypothesis of the current study is  $H_0: HR = 1$  vs.  $H_1: HR \neq 1$  ; and HR is the hazard ratio of treatment compared to control arm.

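### The primary efficacy set excludes patients on two events after open-label randomisation, one of which almost only the experimental arm can fail, so the primary test can be biased

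*Protocol*

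**What the plan says.** Section 9.1 names two sets. The first is complete: "The Intention to treat (ITT) analysis will include all subjects randomized". The second is the one used: "The primary analysis population for the evaluation of both efficacy and safety outcomes will be a modified ITT population". A patient belongs to it if randomised, "in which the study drug (Favipiravir tables + Hydroxchloroquine or Standard of care") "was started and the patient did not withdraw consent". The start condition is worded for both arms, and no time limit is put on withdrawal of consent.

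Section 9.2.1(d) confirms the consequence for non-starters and gives the only indication of their number: "It is anticipated that very few of these subjects will be randomized and not start study treatment (and so be excluded from the primary analysis"). Under section 9.4, patients who were randomised but not treated are described by deaths, SAEs and the reason for non-treatment. The same section censors patients lost to follow-up at their last contact.

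Three features of the design bear on this:

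- Blinding (section 3): "This is an Open label, multicenter, randomized controlled clinical trial".
- Control treatment (Reference Therapy, under section 6): "Standard care comprised, as necessary, supplemental oxygen" and other support.
- Timing (Treatment assignment): "The possible study participant can be assessed in the first 72 hours of admission regarding eligibility".

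**The concern.** Randomisation makes the arms comparable only for the set that was randomised. Here the primary set depends on two later events, and patient and physician both know the arm when those events occur.

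The start condition is unequal in effect, although equal in wording. A control patient is already in hospital and receiving supportive care as needed, so it is hard to see how standard of care could fail to start. In the experimental arm there is a gap between allocation and first dose: the flow chart places randomisation on D0 or D1 and both drugs from D1. A patient who deteriorates, dies or refuses in that gap leaves the primary set, while the matching control stays in. If such patients tend to improve slowly, the experimental arm looks better without any drug effect.

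The consent condition applies to both arms. As worded, a patient who withdraws drops out of the primary set, whereas one lost to follow-up stays in and is censored. Two similar kinds of dropout are treated differently, and withdrawal can be related to how the patient is doing.

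The primary p-value is at stake, and with it the interim efficacy, futility and sample-size decisions in section 9.3, which names no other population.

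**Working it through.** **1. The plan's own figure.** Inputs from section 9.2: HR 0.7, one-sided alpha 0.025, power 85%, 1:1 allocation, event proportions 50% and 70% (mean 60%).

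- Events (Schoenfeld): 4 × (1.960 + 1.036)² / (ln 0.7)² = 282.3, so 283.
- Patients: 283 / 0.60 = 471.7, so 472 (236 per group), as stated.
- With 10% added: 236 × 1.10 = 259.6, so 260 per group and 520 in total, as stated.

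The sample size reproduces and does not depend on this point.

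**2. What an exclusion share means.** Of 260 experimental patients, 1% is about 3, 2% about 5 and 5% is 13. The dropout allowance for non-starters and losses together is 520 − 472 = 48 over both arms.

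**3. Size of the possible bias.** The protocol gives no exclusion rate by arm and no prognosis for excluded patients, so both are assumptions. The illustration is a log-rank simulation with 260 per arm, no true effect, exponential times, censoring at day 28 and 4,000 to 8,000 runs per scenario. A share of slow improvers exists in both arms and is removed from the experimental arm only. Nominal one-sided error is 2.5%.

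Section 9.2.1 supports two control assumptions that differ under an exponential model. An 11-day median gives 1 − 2^(−28/11) = 83% improved by day 28, whereas item (c) assumes 50% improved. Both were used.

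| Improvement rate of excluded patients | Share excluded | 11-day median | 50% improved by day 28 |
|---|---|---|---|
| Half the usual rate | 1% | 3.0% | 2.7–2.8% |
| | 2% | 3.6% | 3.0–3.2% |
| | 5% | 5.4–5.6% | 4.0–4.5% |
| One-fifth of the usual rate | 1% | not run; between 3.0% and 3.7% | 3.2% |
| | 2% | 4.4–4.8% | 3.5–4.2% |
| | 5% | 10.2–11% | 6.1% |
| Never improve by day 28 (extreme) | 1% | 3.7% | 3.0% |
| | 2% | 6.6% | 4.2% |
| | 5% | 18.4% | 8.0% |

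Ranges within a cell are results of separate runs. With no exclusions the simulation returns 2.4–2.8%; simulation error is about 0.2 percentage points near 2.5%. At 5% excluded, one-fifth rate and 11-day median, the apparent hazard ratio for improvement under the null is 1.07.

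Contrasting cases:

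- Exclusion unrelated to prognosis, 5%: 2.6–2.7%.
- Slow improvers excluded equally, 3% in each arm: 2.3–2.8%.
- Patients improving twice as fast excluded from the experimental arm, 3%: 1.4–1.5%, which is conservative.

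**4. Power if ITT is primary.** Let a share x of the experimental arm never start and behave like controls. Events are 130 + 260 × [0.7(1 − x) + 0.5x], and the log hazard ratio shrinks to (1 − x) × ln 0.7. Power is Φ(√events / 2 × |log HR| − 1.960).

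- x = 0: 312 events, power 88.3%.
- x = 2%: 311.0 events, HR 0.705, power 86.9%.
- x = 5%: 309.4 events, HR 0.713, power 84.6%.

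If a further 10% are lost in both arms, these become 84.8%, 83.2% and 80.7%. That is pessimistic, because the 10% allowance already includes non-starters.

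**The case against.** The protocol expects very few non-starters, and only the interval from allocation to first dose is exposed. Patients who start and then stop remain in the set. Many reasons for not starting should appear before randomisation: QTc, QT-prolonging drugs, severe liver damage and advanced kidney disease are eligibility criteria, and ECG and laboratory tests are scheduled on D0 as well as D1. Nasogastric administration is described for both drugs. Refusal of tablets need not signal a poor prognosis. The all-randomised analysis is defined, so it can be shown beside the primary one. All of this stands, and it limits the likely size. It does not remove the fault: the rule is a stated choice, and if non-starters are very few, excluding them gains almost nothing.

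Three stronger readings are tempting, and the documents do not support them.

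- **Both conditions remove patients almost only from the experimental arm.** This is a fair inference for the start condition only. The consent condition applies to both arms, no split is given, and controls who learn that they did not receive the drugs may also withdraw.
- **The rule deletes data already collected from patients who withdraw.** Section 9.1 leaves these patients out of the primary set. It says nothing on the timing of withdrawal or on the use of earlier data.
- **Type I error is 11%.** That needs 5% one-sided exclusion, one-fifth the improvement rate and the 11-day median. With the protocol's own 50% control proportion the same case gives about 6%.

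The simulation is also a single-stage test, not the two-stage sum of p-values planned in section 9.3.

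**Conclusion.** The point holds as a risk of bias, not as a demonstrated bias. Section 9.1 makes the primary efficacy comparison depend on two events after open-label allocation, and the start condition can in practice be failed almost only in the experimental arm. If slow improvers are lost from that arm only, one-sided type I error is about 3% at 1% excluded, 3–5% at 2% and 4–11% at 5%. This range runs from half to one-fifth of the usual improvement rate and covers both control assumptions. The error stays nominal if exclusion is unrelated to prognosis, and the test becomes conservative if good-prognosis patients are excluded. The number and prognosis of excluded patients are assumptions throughout. The change is still worth making, because the all-randomised set is already defined and using it costs little.

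**What to change.** In section 9.1:

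- Make the ITT set (all randomised patients, analysed as allocated) the primary population for efficacy.
- Keep data up to withdrawal of consent where consent allows, and censor there, in line with the handling of losses in section 9.4. State that this assumes withdrawal is non-informative; if it is related to prognosis, some bias remains.
- Retain the modified ITT set as a sensitivity analysis.
- Report the number of exclusions, with reasons, by arm.

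Bring section 9.2.1(d) into line, since it now says that non-starters leave the primary analysis.

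The change takes a few sentences and needs no new patients. The cost is slight dilution if some experimental patients never start: with all 520 analysed, power is about 87% at 2% non-starters and 85% at 5%, against the planned 85%.

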| Safety End Points   | This study will be able to determine the safety of investigational therapeutics to determine if the rate of AEs is higher, lower, or no different than control arm.                                                                                                                                                                                                                                                                                                                                                                                                                                                                                                                                                                                                                                                                                                                                                                                                                                                                                                                                                                                                                                                                                                                             |

|                               |                                                                                                                                                                                                                                                                                                                                                                                                                                                                                                                                                                                                                                                                                                                                                      |

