### 7.1 Screening/Baseline

In the participating site, the research coordinator/ delegated study personnel for the site will check all positive reported COVID-19 by PCR confirmed SARS-coV-2 viral infection. Then an assessment of the eligibility by the research coordinator and assessing inclusion/exclusion criteria. The possible study participant can be assessed in the first 72 hours of admission regarding eligibility. Once eligible, informed consent will be obtained. Randomization will be done in 1:1 whether to intervention or control arm and stratified by the center.

Daily assessment and data reporting will be done by the research coordinator/ delegated study personnel including the side effect using the included CRF.

While the management will be done by the treating physician and even stopping the medication in case of concerns. Stopping the interventional medication need to be justified; where a form would be filled.

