### For secondary endpoints:

- Quantitative variables such as duration of ICU stay and change from baseline in clinical scores, etc., are expected to have reasonably skewed distributions and may be subject to censoring (e.g., for subjects in hospital on Day 28; these will be compared between randomized arms using non-parametric tests (e.g., Wilcoxon's Test adapted, if necessary, to handle censoring).
- Analysis of the ordinal scale endpoints will use a proportional odds model with an indicator variable for randomized treatment. The Wald test will be used to generate a p-value comparing treatments, as well as the estimated proportional odds ratio comparing treatments with associated 95% CI.

- Analysis of AE data will primarily be descriptive based on MedDRA coding of events. The proportion of subjects experiencing an SAE and the proportion experiencing a Grade 3 or higher AE will be compared between randomized arms using Fisher's Exact Test.

For enrolled subjects who were not randomized (i.e. screen failures) or who were randomized but did not receive the treatment, the final analysis will detail safety (deaths and SAEs), and reasons they were not randomized or did not received treatment respectively.

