#### 10.4 Handling of Serious Adverse Events

All adverse drug events encountered during the clinical study will be reported on the CRF. Serious adverse events (SAEs), whether or not associated with study medication administration, will be recorded both on the Adverse Event form of the CRF as for non-serious AE and the SAE form.

ALL SAEs occurring during this study and up to 30 days after a subject discontinued or completed the study, whether or not related to the administration of study medication, must be reported by faxing the completed SAE form, after reviewing the report for consistency and accuracy within 24 hours of awareness by the investigator, to KAIMRC / IRB.

As far as possible, investigators should follow-up participants with AEs until the event is resolved or until, in the opinion of the investigator, the event is stabilized or determined to be chronic. Details of AE resolution must be documented in the CRF. Participants should be followed-up for 30 days after receiving the last dose of study medication and any AEs, which occur during this time, should be reported according to the procedures outlined above. Any significant changes in AEs should be reported even though the subject has completed the study, including the protocol-required post-treatment follow-up.

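### Section 9.1 drops treated patients who withdraw consent from the primary safety population, along with adverse events recorded before they withdrew

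*Protocol*

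**What the plan says.** Section 9.1 names two populations. The ITT set holds everyone randomised. The second set is given the main role: "The primary analysis population for the evaluation of both efficacy and safety outcomes will be a modified ITT population". To be in it, a patient must be randomised, the assigned treatment (combination or standard of care) must meet the condition that it "was started and the patient did not withdraw consent". The consent condition carries no time limit, no reason and no reference to permission to use data.

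Section 9.4 (secondary endpoints) then sets the formal safety analysis: "The proportion of subjects experiencing an SAE and the proportion experiencing a Grade 3 or higher AE will be compared between randomized arms", by Fisher's exact test. It names no other population. Its closing paragraph adds a separate safety account for screen failures and for those "who were randomized but did not receive the treatment, the final analysis will detail safety (deaths and SAEs").

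The Protocol Summary gives the purpose of the safety endpoint: to "determine if the rate of AEs is higher, lower, or no different than control arm".

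**The concern.** A safety population normally keeps everyone exposed to treatment, because leaving the trial can itself be a result of harm. Here one set serves both efficacy and safety, and its consent condition acts on patients already under treatment. Suppose a patient takes both drugs, has a Grade 3 event on day 3 and withdraws consent on day 4. That patient is outside the primary safety comparison, and so is an event recorded while consent was in force.

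The trial is open-label, so patients know what they are taking. If withdrawal follows toxicity and is more common on the combination, the combination will look safer than it is. The protocol does not show that this will happen. Under Reference Therapy, controls may receive hydroxychloroquine or other antivirals and may react to those, so the direction cannot be known in advance.

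**Working it through.** **Does any other section restore these patients?**

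| Place | What it does | Restores treated patients who withdraw? |
|---|---|---|
| 9.1, modified ITT | Requires treatment start and, separately, no withdrawal of consent | No, it removes them |
| 9.1, ITT | Defined as all randomised | Contains them, but is not assigned to safety |
| 9.4, Fisher comparison | Names no population, so the 9.1 primary set applies | No |
| 9.4, closing paragraph | Covers patients not randomised or not treated | No |
| 10.3 and 10.4 | AEs go on the CRF; reporting covers "ALL SAEs occurring during this study and up to 30 days after a subject discontinued or completed the study" | No, this governs collection and not analysis |
| 9.2.1(d) | Expects very few to "be randomized and not start study treatment (and so be excluded from the primary analysis") | No, it names only non-starters as excluded, so 9.1 goes further than this account |

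Patients who only stop the drug are not affected. Section 7.1 (Screening/Baseline) lets the treating physician stop it ("Stopping the interventional medication need to be justified; where a form would be filled"), and Section 7.3 requires stopping when QTc exceeds 500 ms. These patients have not withdrawn consent and stay in the set.

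**Arm size used below.** The protocol's own figure reproduces:
- events = 4(1.960 + 1.036)² / (ln 0.7)², which rounds up to 283
- 283 / 0.60 (the mean of 50% and 70%) = 472, or 236 per arm
- 236 × 1.10 = 259.6, or 260 per arm

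The point itself does not depend on this calculation.

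**Illustration of size.** The protocol states no SAE or Grade 3+ rate and no rate of consent withdrawal. Its nominal 10% drop-out covers non-start and loss to follow-up. All event rates here are therefore assumed. Take 260 per arm, with x events on the combination and y on control. Remove k combination patients who each had an event:

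rate = (x − k) / (260 − k), two-sided Fisher exact test against y/260.

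| k removed | 52 v 26 (20% v 10%) | 65 v 39 (25% v 15%) | 26 v 13 (10% v 5%) |
|---|---|---|---|
| 0 | 20.0%, p=0.002 | p=0.006 | p=0.045 |
| 1 | 51/259 = 19.7%, p=0.002 | p=0.006 | p=0.045 |
| 3 | 49/257 = 19.1%, p=0.004 | p=0.011 | p=0.086 |
| 5 | 47/255 = 18.4%, p=0.008 | p=0.019 | p=0.16 |
| 13 | 39/247 = 15.8%, p=0.06 | p=0.083 | p=1.00 |

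Power at true rates of 20% v 10% was found by exact enumeration of both binomials, counting Fisher p<0.05 with the combination rate higher. It is 87.4% with all treated patients. With k = 1, 3, 5 and 13 removed it is 87.4%, 82.5%, 76.0% and 46.6%.

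**Cases that point the other way, at 52 v 26:**
- Balanced: 10% of affected patients removed from each arm (5 and 3) gives 47/255 v 23/257 = 18.4% v 8.9%, p=0.002.
- Average risk: 13 combination withdrawals, 3 with an event, gives 49/247 = 19.8%, p=0.003.
- No events: 13 combination withdrawals without an event gives 52/247 = 21.1%, p=0.0008.

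**The case against.** The best counter-argument is that the clause was meant narrowly: withdrawal before treatment, or withdrawal of permission to use data. Section 9.2.1(d), which lists only non-starters as excluded from the primary analysis, can be read that way. But a patient who withdraws before starting already fails the treatment-start condition, so on that reading the consent clause would do nothing. The data-use reading is possible, but the text does not state it. If that was the intent, the same sentence should be corrected to say so.

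The ITT set contains these patients, so an ITT safety analysis could still show their events. That is true, and it limits the point to the primary safety analysis. The protocol does not say that such an analysis will be done.

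A consent condition can have a legitimate use. Section 11.3 allows surrogate consent, and enrolment on the attending physician's consent, with the patient told later. Whether data collected before withdrawal may be kept depends on consent wording not seen here. This stands as a limit on the fix: patients who forbid use of their data must be left out.

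Patient protection does not rest on this set, since SAEs are reported within 24 hours and the DSMB sees unblinded data. AE analysis is mainly descriptive. At 20% v 10%, significance is lost only in the extreme case of 13 one-sided removals, all with events. The 10% v 5% example is borderline from the start. All of this stands and keeps the point moderate.

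Detail such as the data cut-off could go in the SAP. The population rule, however, is fixed in the protocol, and an SAP that followed it would carry the exclusion forward.

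**Conclusion.** The point holds. As worded, Section 9.1 makes membership of the primary safety population depend on a post-treatment decision that adverse events can influence, and nothing else in the protocol reverses this. The practical size is unknown. With one to three affected patients it is small unless events are rare. It becomes material only if a larger number withdraw, mostly after events and mostly from one arm. The direction is also unknown. The conclusion rests on the plain reading of the consent clause as unlimited in time, and the numbers rest on assumed event and withdrawal rates. The change is worth making because the rule bears on a stated safety endpoint and is cheap to correct.

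**What to change.** In Section 9.1, define a separate safety set: all randomised patients who started their assigned treatment, with controls counted from randomisation. Remove the consent condition for safety. State that all AE, SAE, laboratory and ECG data recorded up to the date of withdrawal are used. Tabulate by arm how many patients withdrew consent and whether an AE came first.

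The cost is one sentence in 9.1 and one table row, using data already on the CRF. There are two drawbacks. Patients who withdraw have shorter observation, and those who forbid use of data already collected must be left out and counted by arm.
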